### Outcome measurements

Criteria for the selection of the outcome measurements are reliability, validity and sensitivity for statistical change.

#### Primary outcome

**Patient-specific LBP-related disability **will be assessed using the patient specific functional scale (PSFS), a self-reported measurement for up to three individual activity limitations rated on an 11-point numeric rating scale ranging 0-10 [56]. Measurement is taken at baseline, post-treatment, and at 6 and 12 months follow-up. Reliability and validity have been reported to be good [57,58]. Internal and external responsiveness are good, indicating that the test detects a change in active limitation and that this change is meaningful [59]. In patients with low levels of activity limitations, the PSFS has better responsiveness than the RMQ [60].

#### Secondary outcomes

**General LBP-related disability **will be assessed with the RMQ [54]. It consists of 24 dichotomous questions to be answered with yes or no, and has a maximum disability score of 24 points. Measurement is taken at baseline, post-treatment and at 6 and 12 months follow-up. Reliability and validity have been widely tested, reliability is high, and construct and internal validity are good [61]. The reliability and validity of the German version have been confirmed [48].

**Pain, daily activities, social participation and professional participation **will be assessed using the Graded Chronic Pain Scale (chronic pain grade = CPG) [62]. The German version of the questionnaire shows significant correlations with other assessments of disability and staging of chronic pain, and a good internal consistency (Cronbach's alpha = .82) [63]. Measurement is taken at baseline, post-treatment, and at 6 and 12 months follow-up. Sports and leisure activities will be assessed with a self-administered questionnaire developed for this study.

**Range of motion **is measured pre- and post-treatment by finger to floor distance, a valid, reliable and responsive measurement correlating with radiography in patients with chronic low back pain [64].

**Tactile acuity (two point discrimination TPD) **is measured in the paravertebral lumbar region using a plastic caliper ruler between L1 and the iliac crest. Measurements are taken horizontally and vertically. The two point discrimination threshold is where the smallest distance at which the patient correctly reports feeling two points of the caliper instead of one is located. We will calculate the average of two procedures; one starting with an extended position of the calipers with the distance being decreased, the other starting with calipers in a contracted position and the distance being increased. Out of sequence tests are performed to avoid the recognition of a pattern. This test was recently used in patients with NSLBP [30]. Reliability was not formally evaluated in this population. TPD is measured pre- and post-treatment.

**Direct and indirect LBP related costs **will be calculated based on the use of medication and medical treatment. Data are recorded according to information given by the patient. Indirect costs are calculated in sick leave days costs based on Swiss average salary data (Statistisches Jahrbuch der Schweiz, 2011).

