### Participants and recruitment

Admission criteria for the study are described in Table 2. Eligible are patients with NSLBP referred to physiotherapy by their physician. Patients will be recruited by the participating physiotherapists. Patients are included in the study if at least 2 MCI tests are positive and if they present clinical symptoms of MCI as described by [21,24,25,27,30,36]. Patients with specific LBP, identified by the physician or by the physiotherapist are excluded from the study. To prevent floor effects in outcome measurement, a minimal disability of 5 points on the Roland and Morris Disability Questionnaire (RMQ) [54] is required. Excluded are patients with predominant psychosocial factors, defined as a score of more than 130 points on the Örebrö Musculoskeletal Pain Questionnaire (ÖMPQ) [51,52]. An ÖMPQ score of over 130 has been shown to correctly predict failure of return to work in 86% of cases [51]. The German version of the ÖMPQ has been used in a previous study in Switzerland [55].

**Table 2 T2:** Inclusion and exclusion criteria

Inclusion criteria	- Age 18 to 75 years - Non-acute LBP (> 6 weeks duration of symptoms) and less than 3 months of sick leave due to LBP - Two or more positive tests for impaired movement control (Luomajoki et al 2007) - At least 5 points on Roland Morris Disability questionnaire [54] - Clinical behaviour: posture and movement aggravate and ease symptoms; symptoms are relieved by reducing the strain on the lumbar region - Written informed consent
Exclusion criteria	- Specific LBP (Fractures, carcinoma, anomalies, nerve root affection with neurological signs e.g. sensitivity or reflex loss, muscle weakness, radicular pain below the knee) - Less than 6 weeks post-surgery following all surgery on the lower back - post-surgery with spondylodesis - high level of psychosocial risk factors (> 130 points on the ÖMPQ) - Peripheral or central neurological disease - Contraindications for exercise, e.g. major cardiovascular disease or postural hypotension - Inability to understand the purpose of the study - Psychological or psychiatric problems - Chronic abuse of toxic substances such as drugs or alcohol - Use of neuroleptics, sedatives, anti-epileptics and antidepressants

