### Treatment effect modifiers

The following relevant covariates will be recorded in order to allow them to be controlled for in the analysis of this study. Movement control and endurance are addressed in the two treatment groups and are expected to modify treatment effect.

**Movement control impairment **of the lumbar spine is assessed using 6 tests described in the backgrounds section [65]. Post-treatment the test will be recorded on videotape. The evaluation of video footage will be carried out by a specially trained physiotherapist who will be blinded to the treatment allocation and data from previous measurements.

**Endurance of lumbar and abdominal muscles **is assessed using static isometric strength tests for trunk extension and for trunk flexion pre- and post-treatment [66,62].

**Fear avoidance beliefs **will be measured with the self-report Fear-avoidance beliefs questionnaire for physical activities and work developed by Waddell et al [67,68]. The validated Swiss German Version will be used, allowing prediction of treatment outcome [67] It will be administered at baseline.

Patient's regular use of **home exercises **will be assessed at 6 and 12 months follow-up.

**Personal characteristics **(age, gender, previous episodes of back pain) will be collected at baseline.

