### Data analysis

The comparability of both groups on prognostic and outcome variables at baseline will be analysed using two-sample t-tests in data with a normal distribution, Wilcoxon tests in non-parametric data and Chi-square tests in nominal data. An intention-to-treat analysis will be utilised in which all participants will be analysed in the group to which they were originally assigned. Differences between the groups over time are measured by Mann-Whitney-U-test. The influence of baseline differences on outcome measurements will be assessed in a multivariable linear regression analysis. A regression analysis of the factors being positive or negative predictors will be conducted based on covariates measured at baseline. Statistical significance is set at p < 0.05.

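### Low back pain sick leave before entry is checked for eligibility but is not listed as a covariate for the indirect-cost outcome; the cost is some precision, not bias

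*Protocol article*

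**What the plan says.** Four places in the protocol article bear on this.

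- **Secondary outcomes (costs).** Indirect cost is sick-leave days priced at a national average wage: "Indirect costs are calculated in sick leave days costs based on Swiss average salary data". The source is patient report: "Data are recorded according to information given by the patient". No time points, baseline period or counting window are given for costs, whereas the questionnaires and physical tests in the same section mostly have theirs.
- **Participants and recruitment, Table 2.** One inclusion criterion is "Non-acute LBP (> 6 weeks duration of symptoms) and less than 3 months of sick leave due to LBP". A patient may therefore enter with no absence or with any amount short of three months.
- **Treatment effect modifiers.** The list opens with its purpose: "The following relevant covariates will be recorded in order to allow them to be controlled for in the analysis of this study". It names movement control, endurance, fear avoidance, home exercise and personal characteristics, the last given as "age, gender, previous episodes of back pain) will be collected at baseline". Neither sick leave nor work status appears.
- **Data analysis.** The arm comparison is stated as "Differences between the groups over time are measured by Mann-Whitney-U-test". Before that comes a general baseline check, "The comparability of both groups on prognostic and outcome variables at baseline will be analysed". After it come two regressions: one on the influence of baseline differences on outcomes, the other on predictors among covariates measured at baseline.

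**The concern.** Sick leave before entry is the natural baseline counterpart of an outcome made of sick-leave days. Someone off work at randomisation is likely to carry some absence into follow-up in whichever arm they join. The question has to be asked at entry to apply Table 2, but nothing says the answer is kept as a number of days, and the covariate list omits it.

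Two things are at stake, both confined to the cost outcome. First, a few long absences can supply a large share of all days, so their chance split between arms adds noise that a baseline covariate would remove. Second, the Mann-Whitney test compares ranks, whereas a cost outcome is usually read as a difference in mean cost per patient, the quantity most sensitive to those few patients.

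**Working it through.** The article gives no figure for sick leave or costs, so there is none to reproduce. It supplies the group size (48 per arm needed, 106 randomised, hence 53 per arm) and the entry limit (under three months). Every distribution below is an assumption.

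**Check 1: closed form.** Let p be the share off work at entry, with mean μ1 and SD σ1 follow-up days. The rest have mean μ0 = 4 and SD σ0 = 12. With n = 48 per arm:

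- unadjusted variance per patient: V = pσ1² + (1−p)σ0² + p(1−p)(μ1−μ0)²
- variance after adjusting for off-work status: W = pσ1² + (1−p)σ0²
- standard error (SE) of the arm difference: √(2V/48) or √(2W/48)

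For p = 0.10, μ1 = 60, σ1 = 40:

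- W = 160 + 129.6 = 289.6
- V = 289.6 + 0.09 × 56² = 571.8
- SE = √(2 × 571.8/48) = 4.88 unadjusted and √(2 × 289.6/48) = 3.47 adjusted

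| Assumed off-work group | p | SE unadjusted | SE adjusted | Reduction |
|---|---|---|---|---|
| mean 60, SD 40 | 0.05 | 3.90 | 3.01 | 23% |
| mean 60, SD 40 | 0.10 | 4.88 | 3.47 | 29% |
| mean 60, SD 40 | 0.15 | 5.64 | 3.89 | 31% |
| mean 30, SD 30 | 0.05 | 2.99 | 2.75 | 8% |
| mean 30, SD 30 | 0.10 | 3.42 | 3.03 | 11% |
| mean 30, SD 30 | 0.15 | 3.78 | 3.27 | 13% |

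**Check 2: simulation under different assumptions.** There are 106 patients, 53 per arm under simple allocation (the blocks of four were not modelled). Of these, 5, 10 or 20 bring 5 to 90 days of earlier leave, and 15% have new leave averaging 20 days. The SD of the arm difference, in days per patient, was:

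| Correlation of earlier with follow-up leave | Unadjusted | Adjusted | Reduction |
|---|---|---|---|
| 0.3 | 2.14–2.17 | 2.04–2.07 | 4–5% |
| 0.5 | 2.31–2.39 | 2.01–2.05 | 13–14% |
| 0.7 | 2.84–2.93 | 2.03–2.11 | 26–30% |

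**Check 3: how uneven the split can be.** With 53 per arm and 4, 6, 10 or 20 patients with earlier leave, the hypergeometric probability that the arms differ by at least 4 such patients is 0.12, 0.21, 0.32 or 0.46. For 10 patients this means 7:3 or more uneven. Under the 60-day assumption, a 7:3 split alone shifts the difference in means by 4 × (60 − 4)/48 = 4.7 days per patient. The unadjusted 95% half-width at p = 0.10 is 1.96 × 4.88 = 9.6 days, so the shift is about half of it.

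**Check 4: the rank test.** Suppose all 10 outrank everyone else and split 7:3 with 48 per arm. The probability that a patient in one arm exceeds one in the other moves by (4/48)/2 = 0.042. Without ties its null standard error is √(97/(12 × 48 × 48)) = 0.059, so z is about 0.7. If the other 86 patients all have zero days, the tie correction raises z to about 1.3. Neither reaches significance.

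**The case against.** The strongest reply is that the article never describes the cost comparison. It says how days are priced and stops there. It condenses a fuller protocol, and the covariates for one secondary outcome may be set out there or in an analysis plan. This stands in part. A reader might infer that the plan commits to comparing costs without entry sick leave, but the documents do not say so. The regression on baseline differences is worded generally and could take in sick leave if the item were kept. What remains is that the article does set out a list of covariates to be recorded for control, and this one is not on it.

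A reader might also infer that the item is collected and then discarded. Table 2 sets only a threshold, and nothing shows that a day count or off-work status is recorded.

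Other points for the plan also hold. The fear-avoidance questionnaire covers work, and the graded chronic pain scale captures professional participation at baseline, so partial proxies exist. Patients scoring above 130 on the Örebro questionnaire are excluded, and the article links that cut-off to failure to return to work. Long absences may therefore be fewer than the 60-day assumption implies. The rank test also limits the pull of extreme patients, although it does not give a difference in mean cost.

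**Conclusion.** The point holds as a modest one. Entry sick leave is checked, it is the obvious baseline counterpart of the indirect-cost outcome, and it is not among the covariates listed for control. The only named arm comparison is unadjusted and rank-based. The loss is precision and exposure to chance imbalance, about 5% to 30% of the standard error. Where it falls in that range depends on the prevalence of earlier absence and its correlation with later absence, neither of which the documents give.

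The stronger reading, that a chance split of a few patients biases or dominates the cost result, is not supported. Random allocation leaves the unadjusted difference unbiased, and its interval already allows for chance imbalance. Even under the heavier assumption, a 7:3 split moves the mean difference by only about half the 95% half-width. Costs appear in neither hypothesis, and the primary outcome is untouched. Priority is optional to low.

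**What to change.** 1. From the eligibility check, record the number of low back pain sick-leave days before entry, and whether the patient is off work at randomisation, as baseline variables. Add both to the list under Treatment effect modifiers. Recruitment began in July 2010, so for patients already enrolled the values should come from eligibility records where these exist, not from later recall.
2. State that only sick-leave days after randomisation count towards indirect cost, and over what period.
3. Estimate the arm difference in mean sick-leave days and mean indirect cost with entry sick leave as a pre-specified covariate and a bootstrap interval. Report the unadjusted difference beside it.

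The cost is a few lines of analysis text and carrying the eligibility answer into the dataset, as a day count and a work status instead of only a pass or fail. No extra patients or visits are needed. The downside is one more model term for a skewed secondary outcome.

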### Treatment effect modifiers

The following relevant covariates will be recorded in order to allow them to be controlled for in the analysis of this study. Movement control and endurance are addressed in the two treatment groups and are expected to modify treatment effect.

**Movement control impairment **of the lumbar spine is assessed using 6 tests described in the backgrounds section [65]. Post-treatment the test will be recorded on videotape. The evaluation of video footage will be carried out by a specially trained physiotherapist who will be blinded to the treatment allocation and data from previous measurements.

**Endurance of lumbar and abdominal muscles **is assessed using static isometric strength tests for trunk extension and for trunk flexion pre- and post-treatment [66,62].

**Fear avoidance beliefs **will be measured with the self-report Fear-avoidance beliefs questionnaire for physical activities and work developed by Waddell et al [67,68]. The validated Swiss German Version will be used, allowing prediction of treatment outcome [67] It will be administered at baseline.

Patient's regular use of **home exercises **will be assessed at 6 and 12 months follow-up.

**Personal characteristics **(age, gender, previous episodes of back pain) will be collected at baseline.

### Interventions

Assessors and treating physiotherapists in both groups are trained for at least 4 hours and receive a manual containing descriptions of procedures and checklists. To support adherence to the treatment procedures, a structured recording form is provided. This study uses a pragmatic approach to treatment progression in both intervention groups. The therapist responsible for treatment has to select from exercises permitted for the relevant treatment group. The exercise prescription for the individual patient is determined by the clinical judgement of the therapist. Patients in each group will be treated by their specially trained physiotherapists in individual 30 minute sessions. Patients will receive 9-18 treatments within a period of 12 weeks. The number of treatments will be recorded. At least 20 minutes of each session are to be used for exercise according to the protocol. If required, a maximum of 10 minutes can be used for other physical therapy applications. Therapy will be monitored and evaluated using a therapists' treatment diary.

Patients are instructed to do at least three home exercises of either movement control or general exercise. They are strongly encouraged to continue them during the follow-up year. Patients are informed about frequency, number of repetitions and the intensity at which they are to perform the exercises.

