**Methods/Design:**

In a randomised controlled trial (RCT) we will compare the effectiveness of movement control and general exercise in patients with MCI. 106 participants aged 18 - 75 will be recruited in 5 outpatient hospital departments and 7 private practices.

Patients randomly assigned to the movement control exercise group will be instructed to perform exercises according to their MCI. The general exercise group will follow an exercise protocol aimed at improving endurance and flexibility. Patients in both groups will receive 9 - 18 treatments and will be instructed to do additional exercises at home.

The primary outcome is the level of disability assessed using the patient specific functional scale (PSFS) which links the perceived pain to functional situations and is measured before treatment and at 6 and 12 months follow-up. Secondary outcomes concern low back pain related disability (Roland Morris questionnaire, RMQ), graded chronic pain scale (GCPS), range of motion and tactile acuity.

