## Methods/Design

### Design

In this randomised controlled trial we will include patients with non-acute NSLBP and MCI. Patients will be recruited and treated in 5 hospital outpatient departments and 8 private practices in Switzerland. Movement control exercise will be compared to general exercise. Treatment outcomes are to be measured at baseline, post-treatment, and at 6 and 12 months follow-up (Figure 1).

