### Baseline assessment and randomisation

After eligibility has been confirmed, patients will be informed about the study comparing two treatments that are widely used in physiotherapy. After obtaining written informed consent, baseline measurements will be performed (see next paragraph). Participants will then be randomised using block allocation with a block size of four, to receive either movement control or general exercise. Randomisation is concealed and performed by an independent assistant at the School of Health Professions at the Zurich University of Applied Sciences via telephone.

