## Discussion

This randomised controlled trial will compare the effectiveness of two exercise-based physiotherapy treatment protocols in a well-defined subgroup of NSLP. Inclusion is based on the clinical diagnosis of MCI with clinical tests shown to be reliable. The MCI tests allow easily applicable selection of participants. We will evaluate whether a treatment protocol addressing movement control problems is more beneficial than a general exercise protocol.

The multicentre design of the study allows treatment by different physiotherapists and improves generalisability. The selection of patients reflects the population usually found in different clinical settings. Randomisation is organised centrally and prevents selection bias.

Both treatment protocols are widely used and well-established in physiotherapy. The physiotherapists treating each group are equally instructed and experienced in applying the respective treatments. This prevents a disadvantage for the participating patients regarding group allocation.

Blinding the therapists is generally not possible. To minimise measurement bias, the measurements taken after the treatment will be taken by an assessor not involved in the treatment procedures.

The results of this study will provide evidence to improve the selection of exercise treatments for patients with NSLBP and MCI. Results will also contribute to the understanding of the mechanisms behind MCI and its relation to low back pain.

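### Therapist appears nested in treatment arm, yet the named test, the regression and the sample size all treat patients as independent, so p-values may be too small

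*Protocol article*

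**What the plan says.** Under Interventions the article states: "Patients in each group will be treated by their specially trained physiotherapists in individual 30 minute sessions". The Discussion speaks of the therapists in the same way: "The physiotherapists treating each group are equally instructed and experienced in applying the respective treatments". Content is partly individual: "The exercise prescription for the individual patient is determined by the clinical judgement of the therapist". The Discussion counts the variety of therapists as a strength: "The multicentre design of the study allows treatment by different physiotherapists and improves generalisability".

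Allocation is by individual patient: "Participants will then be randomised using block allocation with a block size of four, to receive either movement control or general exercise". The number of sites is 12 in the abstract ("106 participants aged 18 - 75 will be recruited in 5 outpatient hospital departments and 7 private practices") and 13 under Design ("Patients will be recruited and treated in 5 hospital outpatient departments and 8 private practices in Switzerland"). The number of therapists is not given.

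Under Data analysis, the between-group comparison is fixed as follows: "Differences between the groups over time are measured by Mann-Whitney-U-test". A multivariable linear regression handles baseline differences. Therapist is not named there, nor among the covariates listed under Treatment effect modifiers. The sample size section uses a difference of 0.9 PSFS points, SD 1.5, alpha 0.05 and power 0.9, giving 48 per group and 106 in total with 10% drop-out. It contains no allowance for clustering.

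**The concern.** Patients who share a therapist tend to have correlated outcomes, because skill, manner and choice of exercises are shared. If the same therapists served both arms, a therapist effect common to both would largely cancel in the comparison. If each arm has its own therapists, it does not cancel: the arm means differ partly because the therapists differ. Randomising individual patients does not remove this, since patients are randomised to an arm and therapists are not.

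A Mann-Whitney test or ordinary regression then judges the arm difference against patient-level variation only. The standard error is too small, the true type I error exceeds 5% whenever the therapist ICC is above zero, and a difference between two sets of therapists could be read as a difference between two kinds of exercise. The trial's claim to generalise over therapists calls for their variation to be part of the uncertainty.

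**Working it through.** **1. The plan's own figure.** With n per group = 2 × (z_alpha + z_beta)² × (SD/difference)², and difference/SD = 0.9/1.5 = 0.6:
- one-sided alpha 0.05: 2 × (1.645 + 1.282)² / 0.36 = 47.6, so 48, which matches the article;
- two-sided alpha 0.05: 2 × (1.960 + 1.282)² / 0.36 = 58.4, so at least 59, which does not match.

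Drop-out: 48 × 1.1 = 52.8, so 53 per group and 106 in total, which matches. The stated size is thus exactly the figure for independent patients, with a design effect of 1.

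**2. Type I error with therapists nested in arm.** The ICC and the patients per therapist (m) are assumptions. With 48 analysed per arm, m = 48/13 = 3.7 is one therapist per arm at each of 13 sites. m = 8 is 6 therapists per arm. m = 2 allows for several therapists at some sites. Design effect DE = 1 + (m − 1) × ICC; actual two-sided error = 2 × [1 − Φ(1.96/√DE)].

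| Patients per therapist | ICC 0.01 | ICC 0.05 | ICC 0.10 |
|---|---|---|---|
| 2 | DE 1.01, 5.1% | DE 1.05, 5.6% | DE 1.10, 6.2% |
| 3.7 | DE 1.03, 5.3% | DE 1.13, 6.6% | DE 1.27, 8.2% |
| 8 | DE 1.07, 5.8% | DE 1.35, 9.2% | DE 1.70, 13.3% |

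Example: m = 8, ICC 0.05 gives DE = 1 + 7 × 0.05 = 1.35; 1.96/√1.35 = 1.687; error 9.2%.

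**3. Check on the named test.** The Mann-Whitney test was simulated with no true treatment effect, 48 per arm and 6,000 runs per scenario.

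| Therapists per arm | Caseloads | ICC 0 | ICC 0.02 | ICC 0.05 | ICC 0.10 |
|---|---|---|---|---|---|
| 13 | equal | 4.7% | 5.7% | 5.9% | 7.9% |
| 13 | unequal | 4.9% | 6.3% | 8.0% | 10.5% |
| 6 | equal | 4.4% | 6.7% | 8.5% | 12.0% |
| 6 | unequal | 5.3% | 6.8% | 10.3% | 15.3% |

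The rank test behaves as the formula predicts, and unequal caseloads make the inflation worse. A centre effect shared by both arms (ICC 0.10) with no therapist effect gave 4.3% with balanced centres and 4.6% with unbalanced ones, so no inflation.

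**4. Power.** Effective n per arm = 48/DE, two-sided alpha 0.05, noncentral t, standardised difference 0.6. Take m = 4 (12 therapists per arm, 48/12).

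| ICC | DE | Effective n per arm | Two-sided power | Loss due to clustering |
|---|---|---|---|---|
| 0 | 1.00 | 48.0 | 82.9% | none |
| 0.01 | 1.03 | 46.6 | 81.7% | about 1 point |
| 0.05 | 1.15 | 41.7 | 77.3% | about 6 points |
| 0.10 | 1.30 | 36.9 | 72.0% | about 11 points |

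The step from the stated 90% to 82.9% comes from the sidedness of alpha in step 1, not from clustering.

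**The case against.** **Nesting is not certain.** A reader might take it as stated that no therapist treats both arms. The article does not say so. Its wording about choosing among the exercises permitted for the patient's group would also fit a therapist who works in either arm. Separate therapists is the natural reading of both sentences about them, but it remains a reading, and the problem largely disappears if therapists cross arms.

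**Centres are not the cause.** A reader might infer that having 12 or 13 sites without a centre term makes the p-values too small. Patients are randomised individually, and a centre effect shared by both arms did not inflate the error in the simulation. The site count matters only as a rough guide to caseload.

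**No intervals are planned.** The article names tests, regressions and a significance level. Any remark on intervals applies only to those that might be derived from the regression.

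**Power.** A reader might set clustered power against the promised 90% and blame therapists for the whole gap. At low ICC most of that gap is the separate one-sided alpha issue.

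**Therapist discretion is bounded.** Therapists receive training, a manual, checklists and a recording form, and at least 20 of the 30 minutes follow the protocol. This argues for a modest ICC, not for zero.

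**Scope.** A condensed article may leave model terms to an analysis plan. That is fair for the regression. But the article itself fixes a Mann-Whitney test, which has no place for a therapist effect, and a sample size that assumes independence. Those are stated choices, so the point stands.

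**Conclusion.** The point holds in limited form. On the natural reading, therapists are nested in arm, and the analysis and sample size make no allowance for it. Under that reading any positive therapist ICC pushes the error rate above 5%. How far cannot be known from the documents. The inflation is negligible at ICC 0.01 with 2 to 4 patients per therapist (5.1% to 5.3%). It is material at ICC 0.05 with 8 per therapist (9.2%), and more so with few therapists or uneven caseloads. The loss of power due to therapists alone is about 1 to 11 points at 4 patients per therapist, from a two-sided starting point of about 83%. The documents support saying that p-values may be too small, not that they are too small by a known amount.

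**What to change.** 1. State whether any therapist treats patients in both arms, and how many therapists serve each arm.
2. Record an identifier for the treating therapist for every patient. The treatment diary and structured recording form already in use should be able to supply it.
3. Replace the Mann-Whitney test as the primary comparison with a mixed model for PSFS, adjusted for baseline PSFS, with a random therapist intercept (nested in arm, or crossed with arm if therapists treat both) and a small-sample degrees-of-freedom correction. A centre term may be added for precision but is not needed to hold the error rate.
4. Report the estimated therapist ICC with the result.
5. Restate power at the planned 106 patients over an assumed ICC range such as 0.01 to 0.10, showing the no-clustering value beside it and stating whether alpha is one- or two-sided.

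The cost is one data field, one model term and a less favourable stated power. Standard errors will be slightly larger. No change to treatment, randomisation or enrolment is needed.
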